## Abstract

**Background:**

Glioblastoma relapses in the vast majority of cases within 1 year. Maximum safe resection of the recurrent glioblastoma can be offered in some cases. Re-irradiation has been established for the treatment of recurrent glioblastoma, too. In both cases, adjuvant treatment, mostly using temozolomide, can improve PFS and OS after these interventions. However, combining gross tumor resection and adjuvant re-radiotherapy to the resection cavity has not been tested so far.

**Methods/Design:**

In the multicenter two-armed randomized Phase II GlioCave Study, fractionated stereotactic radiotherapy to the resection cavity, after gross tumor resection of recurrent glioblastoma, will be compared to observation. Depending on the size of the target volume, a total dose of 46 Gy in 2 Gy per fraction or a total dose if 36 Gy in 3 Gy per fraction will be applied. Progression free survival will be the primary endpoint of the study.

**Discussion:**

Adjuvant treatment after gross tumor resection of recurrent glioblastoma is currently deemed to be limited to chemotherapy. However, re-irradiation has proven safety and tolerability in the treatment of macroscopic disease. Performing re-irradiation as an adjuvant measure after gross tumor resection has not been tested so far. The GlioCave Study will investigate the efficacy and the safety profile of this approach.

**Trial registration:**

The trial was prospectively registered at clinicaltrials.gov (NCT02715297, registration date February 29th, 2016). The protocol presented hereby refers to the version 1.2 of the protocol (January 11^th^, 2017).

## Background

Glioblastomas (GBM) refer to the most frequent and most aggressive primary brain tumors in adults; they are associated with a significant treatment resistance, in the primary situation as well as in the case of recurrence [1, 2]. Offering an extensive trimodal course of therapies, containing surgery, postoperative radiochemotherapy as well as adjuvant chemotherapy, survival still remains at a poor level. When first published from a randomized study in 2005, the radiochemotherapy regimen with temozolomide (TMZ) elevated median survival from 12.1 to 14.6 months [3]. However, despite extensive research, only minor progress has been achieved since almost 10 years [4–8].

In the vast majority of cases, GBM recurs within 1 year [3], and in most cases recurrence occurs locally [9]. Currently no standard of care can be defined for the treatment of relapsed GBM so far [10]. Thus, patients are treated within individual concepts, mostly based on retrospective studies or small, non-randomized trials [11].

Re-irradiation, especially when modern techniques such as radiosurgery (RS) or fractionated stereotactic radiotherapy (FSRT) has been established in the clinical routine and can be considered a safe and effective alternative for the treatment of recurrent glioblastoma [12–15]. Median overall and progression free survival ranges around 12 and 5 months, respectively, which is comparable to surgery [15, 16]. Generally, re-irradiation is applied in cases with macroscopic tumor remnants, not exceeding a maximum diameter of 4 cm; however, there is much controversy on the ideal target volume, the rationale for imaging during the treatment planning process, as well as to the ideal timepoint of re-irradition. In all cases surgery is evaluated in the case of recurrence, thus is must be discussed whether re-irradiation is only applicable in cases with tumor remnants. To overcome these limitations, it is worth considering multimodal concepts also for recurrent glioblastoma in order to achieve a prolongation of progression free survival.

As a first step, surgery is feasible especially if the tumor recurs in a not eloquent region, in patients with good physical performance status and if the recurrent tumor has a low tumor volume [17]. Furthermore, younger age might be a factor for better outcome [18], yet the prognostic value of second surgery is currently discussed controversially [19, 20].

Combinations of surgery and adjuvant systemic therapy as well as Re-irradiation with concurrent or adjuvant chemotherapy have been reported from several centers [21–24]. Especially the latter was able to achieve median overall survival of up 15 months, counting from the date of radiosurgery, in some series [16]. If only systemic therapy is possible in recurrent GBM due to its location, an early time point after former radiotherapy or the size, then it is associated with an overall survival of 6–8 month [11, 16].

Re-irradiation after surgery was reported to be superior to surgery alone in one prospective cohort, increasing OS from 13 weeks with surgery alone to 34 weeks with surgery plus chemotherapy or radiotherapy as adjuvant treatment [25]. Unfortunately, no target volumes were reported in these series. However, there is no data from randomized trials comparing observation after complete resection to an adjuvant treatment in the same situation. Bimodal local strategies combining complete resection followed by a second course radiotherapy have been reported in the context of brachytherapy, too. The median survival in several studies ranged from 52 weeks to 64 weeks after gross total resection with concurrent implantation of permanent ^125^Iodine seeds [26, 27]. No case of re-surgery for radionecrosis was reported in these two series, rendering adjuvant radiotherapy after GTR of a recurrent GBM as a safe treatment approach. Within a context of high dose rate brachytherapy, the GliaSite system was tested after maximal safe resection of recurrent glioblastoma in small series, gaining an overall survival of 9–13 months [19, 28]. Low dose rate as well as high dose rate brachytherapy are applied directly after surgery, thereby precluding sufficient MRI-based planning. Thus, residual tumor might have received only insufficient doses in this series. This would explain remarkably early progressive disease (16 weeks) described in Larson et al. in 2004 [26].

Within the present GlioCave study, we will investigate the impact of radiotherapy as an adjuvant treatment to patients that underwent gross tumor resection of a recurrent GBM.

## Methods/Design

### Study design

GlioCave is a two-armed randomized multicentre open label phase II trial. Patients fulfilling the inclusion criteria will be 1:1 randomized into two arms (Fig. 1):

**Fig. 1 Fig1:**
[figure not shown]
Flow chart of the GlioCave/NOA-17-Trial

Arm A – Experimental Arm.

Postoperative stereotactic fractionated radiotherapy to a Total Dose of 46 Gy, 2 Gy single dose or 36 Gy in 3 Gy fractions depending in the size and location of the target volume.

Arm B – Standard Arm.

### Observation

Up to 24th April 2017, the study is active in two sides (Munich, Dresden). Activation of more sides is currently under preparation (Regensburg, Heidelberg, Cologne).

### Study objectives and endpoints

The trial is designed to allow the comparison of observation as a standard treatment to adjuvant radiotherapy after GTR of recurrent GBM.

The primary objective of the study is progression-free survival during the follow up phase of at least 12 months. Progression will be defined according to the RANO-HGG as well as to the MacDonald-Criteria [29, 30]. Progression free survival should be preferred as primary endpoint for trials on recurrent glioblastoma as the general aggressiveness of offered treatments influences overall survival in glioblastoma [31]. PFS is thus deemed to be less biased by further therapeutic approaches.

The secondary objectives are overall survival during the follow-up phase of at least 12 months (starting with diagnosis of recurrent disease). Toxicity will be assessed by type, incidence and severity according to the CTCAE v4.02. The EORTC QLQ-C30 version 3.0 questionnaire will be used to monitor for quality of life. Neurocognitive function will be tested at selected centers every 6 months, beginning after randomization. Patients will be followed until death. All study related data will be stored at the MiRO-Database of the Department of Radiation Oncology of the Technical University of Munich.

### Patients

Patients with the diagnosis of recurrent GBM presented will be evaluated and screened for the protocol. All patients fulfilling the inclusion and exclusion criteria will be informed about the study.

#### Inclusion criteria

Unifocal, supratentorial recurrent glioblastomaPrior course of standard treatmentComplete resection of all contrast enhancing areasage ≥ 18 years of ageKarnofsky Performance Score ≥ 60%For women with childbearing potential, (and men) adequate contraception.Ability of subject to understand character and individual consequences of the clinical trialWritten informed consent (must be available before enrolment in the trial)

#### Exclusion criteria

Multifocal glioblastoma or gliomatosis cerebriTime interval of less than 6 months after primary radiotherapyPrevious re-irradiation or prior radiosurgery of prior treatment with interstitial radioactive seedsrefusal of the patients to take part in the studyPatients who have not yet recovered from acute toxicities of prior therapiesKnown carcinoma < 5 years ago (excluding Carcinoma in situ of the cervix, basal cell carcinoma, squamous cell carcinoma of the skin) requiring immediate treatment interfering with study therapyPregnant or lactating womenParticipation in another clinical study or observation period of competing trials, respectively.

### Radiotherapy

Treatment planning will be based on preoperative imaging studies as well as on postoperative MRI and planning MRI.

The clinical target volume (CTV) will contain the margins of the resection cavity of the recurrent tumor, including all contrast enhancing areas +5 mm.

A 1–3 mm expansion will be added to CTV to receive the planning target volume (PTV) depending on individual setup.

Radiotherapy will be prescribed to 95% of the PTV receiving the prescribed dose of either 46 Gy in 2 Gy per fraction or 36 Gy in 3 Gy per fraction.

### Systemic therapy

Chemotherapy is not part of this protocol. However, systemic treatments can be offered to the patients at best investigators choice.

### Statistics

The study is designed to demonstrate that addition of stereotactic fractionated radiotherapy to the resection cavity can significantly improve the progression free survival compared to a maximum safe resectionwithout a further adjuvant radiotherapy (standard treatment).

The data analytical and the statistical aspects of the study will be in accord with the Guidelines of International Conference on Harmonization (ICH):ICH E3: Structure and Contents of Clinical Study ReportsICH E6: Good Clinical Practice (GCP). Consolidated GuidelineICH E9: Note for Guidance on Statistical Principles in Clinical Trials

In the present context we will use an α = 0.1 (one-sided), as a one-sided type I error α = 0.1 presents little risk but increases the statistical power of the study. This is supported by a recent communication from the EORTC [32]. The sample size was calculated assuming a progression free survival (PFS) of 7 months after complete resection of a recurrent glioblastoma (control group) and a PFS of 10 months after additive radiotherapy to the resection cavity. With a planned total trial duration of 48 months, containing a recruitment phase of 36 months and a minimum follow up phase of 12 months and a hazard ration of 0.7, a sample of 81 patients per group is necessary to gain a statistical power of 0.8.

The primary endpoint will be analyzed on the per-protocol-group. Calculations will be made within the SAS-LIFETEST-Procedure. This includes non-parametric tests such as Kaplan-Meier-Estimators as well as lifetime-table-based calculations. Statistics for the secondary endpoint Overall Survival (OS) will be calculated similar.

Secondary endpoints will be described descriptively with the use of a Cox-regression model. Age, Karnofsky Performance Score, Recursive Partitioning Analysis, MGMT-status and initial IDH-1-status will be taken into account for the application of an ingression model.

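### The primary PFS analysis uses only the per-protocol group, although only Arm A has a treatment course to complete; this can bias the test towards radiotherapy and leaves the one-sided 0.10 error unprotected

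*Protocol article*

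**What the plan says.** The Study design section describes the trial: "GlioCave is a two-armed randomized multicentre open label phase II trial", and "Patients fulfilling the inclusion criteria will be 1:1 randomized into two arms". According to the abstract, radiotherapy to the resection cavity "after gross tumor resection of recurrent glioblastoma, will be compared to observation". The Statistics section states a superiority aim, namely to show that added radiotherapy "can significantly improve the progression free survival compared to a maximum safe resectionwithout a further adjuvant radiotherapy (standard treatment".

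The same section then fixes the analysis set: "The primary endpoint will be analyzed on the per-protocol-group". The article does not say who belongs to that group, and it mentions no intention-to-treat analysis, either primary or supportive. After naming the SAS procedure and the Kaplan-Meier and life-table methods, it adds: "Statistics for the secondary endpoint Overall Survival (OS) will be calculated similar".

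The Radiotherapy section sets the Arm A course as the "prescribed dose of either 46 Gy in 2 Gy per fraction or 36 Gy in 3 Gy per fraction". Arm B is observation. Chemotherapy is outside the protocol, but "systemic treatments can be offered to the patients at best investigators choice". That offer is not tied to one arm, so it gives Arm B no assigned course.

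**The concern.** Randomisation makes the arms comparable at the start. They stay comparable only if membership of the analysis set does not depend on what happens later, and a per-protocol set does depend on that. Here the dependence is uneven. An Arm A patient must start and finish a course of several weeks. One who progresses or dies on the way may count as not treated per protocol and leave the analysis. The same patient in Arm B has nothing to complete and counts as an early event. Removing early failures from one arm only makes that arm look better.

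The primary test is at stake. The plan justifies its lenient one-sided 0.10 by saying that it carries little risk. That argument needs an error rate that is actually held at 0.10.

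**Working it through.** **Inputs from the Statistics section.** PFS 7 months (control) and 10 months (radiotherapy), read as medians; HR 0.7; one-sided alpha 0.10; power 0.80; recruitment 36 months plus at least 12 months of follow-up; 81 per group. From the Radiotherapy section: 46/2 = 23 fractions or 36/3 = 12 fractions.

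**Step 1: reproduce the sample size.** Events by Schoenfeld: 4(1.2816 + 0.8416)²/(ln 0.7)² = 142. With exponential PFS and uniform recruitment, the probability of an observed event is 1 − (e^(−12λ) − e^(−48λ))/(36λ), where λ = ln 2/median. This gives 0.917 for a median of 7 months and 0.840 for 10 months, mean 0.878. Then 142/(2 × 0.878) = 80.8, so 81 per group. The stated figure reproduces and leaves no room for excluded patients: 162 × 0.878 is about 142 events, with power 0.801. The number therefore fits an analysis of all 162 randomised patients.

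**Step 2: how many Arm A patients are exposed.** Assume PFS is counted from randomisation with constant hazard (the article gives no PFS start date). With a 7-month median, the share failing before c months is 1 − 2^(−c/7): 4.8%, 9.4%, 13.8% and 18.0% for c = 0.5, 1, 1.5 and 2. If all failures before c are removed, the median of those left is 7 + c months. At c = 2, Arm A would show 9 months against 7 with no treatment effect at all; the planned contrast is 10 against 7.

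**Step 3: type I error.** Simulated trials under no effect, 81 per arm, log-rank test at one-sided 0.10. The exclusion patterns are assumptions, and repeat runs agree to about 0.01.

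| Arm A failures before (months) | Half dropped | All dropped | Apparent HR, all dropped |
|---|---|---|---|
| none dropped | 0.10 | 0.10 | 1.00 |
| 0.5 | 0.14 | 0.18 | 0.95 |
| 1 | 0.16 | 0.27 | 0.90 |
| 1.5 | 0.20 | 0.36 | 0.85 |
| 2 | 0.25 | 0.47 | 0.81 |

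With half dropped before 1.5 or 2 months, the apparent HR is about 0.93 or 0.91.

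**Step 4: vary the mechanism.**
- 10% of Arm A dropped at random: type I error stays at 0.10.
- 5, 10, 15 or 20% of patients have a poorer prognosis (median 3.5 months) and are dropped from Arm A only: 0.14, 0.17, 0.21, 0.26.
- Half of failures before 1.5 months dropped in Arm A and a quarter in Arm B: 0.15.
- Half of Arm A failures before 1 month dropped, plus 20% of Arm B failures before 4 months: 0.09.
- Those Arm B exclusions alone: 0.05, a bias against radiotherapy.

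**Step 5: power if all randomised patients are analysed.** Suppose a fraction f of Arm A goes untreated and has the control hazard. The log hazard ratio shrinks roughly to (1 − f) ln 0.7, and power is about Φ(√142.3/2 × 0.3567 × (1 − f) − 1.2816). For f = 0, 5, 10 and 15% this is 0.80, 0.77, 0.74 and 0.70. Simulation agrees (0.77 to 0.78, 0.74 to 0.75, 0.70 to 0.71 for the last three).

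**The case against.** The strongest reply is that the per-protocol group is undefined in this condensed article. The full protocol may keep patients who stop because of progression or death, which would remove much of the mechanism. That stands as a limit on the size of the bias. It does not rescue the choice, because the article names this set as the primary one and mentions no other.

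Four stronger readings are tempting, and the document does not support them.

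- A reader might infer that the bias must favour radiotherapy. Step 4 shows otherwise: random exclusion does no harm to the error rate, and outcome-linked exclusions from Arm B, for example for off-protocol radiotherapy, can cancel or reverse the bias.
- A reader might infer that the planning MRI gives Arm A an extra way out when it shows regrowth. The Radiotherapy section puts contrast-enhancing areas inside the target volume, and nothing says that such a finding removes a patient from treatment or analysis.
- A reader might infer that overall survival uses the same restricted set. The sentence on OS follows the description of the methods and may refer only to them. It is ambiguous.
- A reader might infer a breach of ICH E9, which the section cites. The article gives only the guideline's title, so its content cannot be checked here, and the point does not need it.

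The largest error rates also need every early Arm A failure to be dropped and none from Arm B, with constant hazard in patients selected for complete resection. The 12-fraction course is shorter, so the lower cut-offs may be the more relevant ones there.

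**Conclusion.** The point holds in this form: a per-protocol set as the only stated set for the primary endpoint of a superiority trial does not protect the type I error, and this design offers a plausible route to bias towards radiotherapy. If early Arm A failures are excluded and comparable Arm B failures are kept, the one-sided error is about 0.14 to 0.25 when half are dropped (cut-offs of 0.5 to 2 months). It is about 0.35 to 0.47 when all are dropped before 1.5 to 2 months. These figures rest on assumed exclusions, exponential PFS and counting from randomisation. Neither the size nor the direction of the bias can be settled from the article. What is settled is that the primary test depends on an undefined selection made after randomisation, in an open-label trial.

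**What to change.** Replace the sentence on the primary analysis set with: *The primary analysis of PFS includes all randomised patients in the arm to which they were randomised (intention-to-treat). OS uses the same set. The per-protocol set, defined in advance, is a sensitivity analysis.* This also removes the ambiguity about OS.

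The change costs one sentence in the protocol and the matching text in any analysis plan, with no extra patients or data; 81 per group can stand. The downside should be stated openly: 81 has no allowance for non-compliance, so if 5 to 15% of Arm A go untreated with control hazard, power is about 0.78 down to 0.70 rather than 0.80. The sponsor can accept that or choose to enlarge the sample.

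### PFS, sized on a hazard ratio of 0.7, has only LIFETEST as its stated method, while the Cox model goes to the secondary endpoints as a block and the covariate model to no named endpoint

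*Protocol article*

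**What the plan says.** All of the analysis text is in the Statistics section of the protocol article.

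- **Design.** The calculation uses a one-sided α of 0.1, PFS of 7 months in the control group and 10 months with radiotherapy, and "a recruitment phase of 36 months and a minimum follow up phase of 12 months and a hazard ration of 0.7". It concludes that "a sample of 81 patients per group is necessary to gain a statistical power of 0.8".
- **Primary analysis.** "Calculations will be made within the SAS-LIFETEST-Procedure". The next sentence describes this as non-parametric tests and gives Kaplan-Meier estimators as the example, with life-table calculations added. OS is to be handled in the same way.
- **Cox model.** "Secondary endpoints will be described descriptively with the use of a Cox-regression model".
- **Covariates.** "Age, Karnofsky Performance Score, Recursive Partitioning Analysis, MGMT-status and initial IDH-1-status will be taken into account for the application of an ingression model". No endpoint is named for this model.

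The secondary-objectives paragraph, under Study objectives and endpoints, begins with OS. It goes on to CTCAE toxicity (kind, frequency and grade), the QLQ-C30 questionnaire, and neurocognitive testing every 6 months at selected centres.

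**The concern.** The trial is designed around a hazard ratio for PFS, yet no estimate of that ratio is assigned to PFS. Kaplan-Meier and life-table methods are estimators, not tests. LIFETEST can also compare the arms, but it does not report the hazard ratio on which the trial was sized.

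The one model that does estimate a hazard ratio is assigned to the secondary endpoints collectively. Of the measures in that paragraph, only OS is an event time. Questionnaire scores, neurocognitive scores and toxicity grades have no event time as defined there, so the rule cannot be carried out for them. Describing endpoints descriptively by means of a regression model is also hard to interpret.

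The plan has already chosen plausible prognostic factors but does not say whether they enter the PFS analysis. Two things are at stake: precision that costs no patients, and protection against deciding on adjustment after the PFS results are known.

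**Working it through.** **Step 1: reproduce the plan's own figure.** The inputs, all from the Statistics section except the allocation ratio (Study design), are HR 0.7, one-sided α 0.10, power 0.80, 1:1 allocation, PFS of 7 and 10 months (taken as exponential medians, so 7/10 = 0.7), 36 months of accrual (taken as uniform) and 12 months of minimum follow-up. No dropout is stated, so it is taken as 0.

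- Events (Schoenfeld): 4(z₀.₉ + z₀.₈)² / (ln 0.7)² = 4(1.2816 + 0.8416)² / 0.1272 = 141.7, so 142.
- Event probability by arm: 1 − (e^(−12λ) − e^(−48λ)) / (36λ), with λ = ln 2 / median. This gives 0.917 (control) and 0.840 (radiotherapy), mean 0.878.
- Patients: 142 / 0.878 = 161.7, or 80.8 per arm, so 81. The plan's figure is reproduced.
- Power with 162 patients: 162 × 0.8784 = 142.3 events, and Φ(√142.3 × 0.3567 / 2 − 1.2816) = 0.801.

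So the sample size follows from an unadjusted proportional-hazards comparison and is not in dispute.

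**Step 2: set the stated methods against the endpoints.**

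| Endpoint | Type of data | Method stated |
|---|---|---|
| PFS | event time | LIFETEST only; no named test, no hazard ratio |
| OS | event time | LIFETEST, then Cox as one of the secondary endpoints |
| Toxicity | frequency and grade | Cox, if counted as a secondary endpoint |
| QLQ-C30 | repeated score | Cox, if counted as a secondary endpoint |
| Neurocognition | repeated score | Cox, if counted as a secondary endpoint |

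OS is sent to LIFETEST shortly before the Cox sentence, and that sentence uses the plural without restriction. Its natural reach is therefore wider than OS.

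**Step 3: what adjustment of PFS could be worth.** The documents give no prognostic effect sizes, so the strength of the covariates is an assumption: a normal prognostic index with the SD shown on the log-hazard scale. The simulations use 81 per arm, control median 7 months, 36 + 12 months, a one-sided test at 0.10, and 0.7 taken as the *conditional* hazard ratio. Three separate runs of 1200, 2000 and 3000 replicates per setting gave the following power (unadjusted log-rank / adjusted Cox). The SD 0 setting was run only with 3000 replicates.

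| SD | 1200 | 2000 | 3000 | Gain (points) |
|---|---|---|---|---|
| 0 | – | – | 0.81 / 0.80 | none |
| 0.4 | 0.733 / 0.793 | 0.73 / 0.77 | 0.74 / 0.79 | 4 to 6 |
| 0.6 | 0.668 / 0.784 | 0.67 / 0.77 | 0.66 / 0.78 | 10 to 12 |
| 0.8 | 0.589 / 0.785 | 0.62 / 0.78 | 0.60 / 0.77 | 16 to 20 |

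In the 2000-replicate run, type I error under a hazard ratio of 1 was 0.09 to 0.11 for both methods. The unadjusted test is valid in every setting.

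**Step 4: what a reported hazard ratio would show.** With 142.3 events the standard error of the log hazard ratio is about 2/√142.3 = 0.168. An observed 0.70 would have an 80% interval of exp(−0.357 ± 1.2816 × 0.168), about 0.56 to 0.87. The stated primary output gives no such figure.

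**The case against.** The strongest reply is that nothing is wrong with the primary comparison. LIFETEST produces log-rank and Wilcoxon tests, the text does mention non-parametric tests, and an unadjusted log-rank test matches the basis of the sample size. A condensed article may leave the name of the test and the reporting of a hazard ratio to the analysis plan. This largely stands: a reader might infer that the plan has no valid primary test, and the documents do not support that.

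A reader might also take the 0.59 to 0.74 in Step 3 to mean that the trial is underpowered. That is not supported either. The plan's 0.7 equals the ratio of the two group PFS values and names no covariates, which points to a marginal ratio. Unadjusted power is then about 0.80 as planned, and adjustment is an improvement, not a repair.

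Two readings of the text must also be held back. The covariate sentence names no endpoint, so the plan does not exclude adjustment of PFS; the link to secondary endpoints rests on position alone. Nor are toxicity, QLQ-C30 and neurocognition individually labelled secondary endpoints, so it is not certain that the authors mean to fit Cox models to scores. A descriptive Cox model for OS only is possible, but the plural and the earlier OS sentence make it the less natural reading.

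What the reply does not remove is the assignment as written: Cox for a mixed block of endpoints, none stated for PFS, and covariates attached to nothing. An analysis plan would have to override this text, not merely add to it.

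**Conclusion.** The point holds as a misassigned model and an avoidable loss of precision. The Statistics section gives the Cox model to endpoints most of which, on the natural reading, cannot be analysed with it. It gives none to the PFS comparison that was sized on a hazard ratio, and it leaves the use of the listed covariates undefined. The primary test is not invalid and the sample size is correct.

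The size of the loss cannot be read from the documents. It is nil if the covariates carry no prognostic information, and about 4 to 20 points of power at assumed SDs of 0.4 to 0.8 if 0.7 is the conditional hazard ratio. If 0.7 is the marginal ratio, the planned power of about 0.80 stands and adjustment could add to it. All of these figures assume that the full 162 patients are analysed with no dropout.

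It should be changed, because the correction is cheap and must be fixed before outcome data are seen.

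**What to change.** 1. Name the PFS test, at one-sided 0.10, and say whether the unadjusted log-rank test or the treatment coefficient of the adjusted Cox model decides the trial. Either is defensible; the log-rank test matches the sample-size calculation.
2. Prespecify a Cox model for PFS, and likewise for OS, with treatment, age, KPS, MGMT and IDH-1 status. Include the Recursive Partitioning class only if it does not duplicate age and KPS. Give missing marker results a category of their own (not known).
3. Report the hazard ratio with a two-sided 80% confidence interval, which corresponds to the one-sided 0.10 level. Label it as conditional on the covariates, and show it beside the unadjusted log-rank result and the Kaplan-Meier curves. Call the latter estimates, not tests.
4. Restrict Cox to PFS and OS. Describe toxicity by proportions at each grade, and analyse QLQ-C30 and neurocognitive scores with methods for repeated scores.

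The cost is wording and a few lines of code, with no added patients. With linear age and KPS and three categories for each marker, the model has 7 parameters (1 treatment + 1 + 1 + 2 + 2), or about 142/7 = 20 expected PFS events per parameter. The real downsides are a conditional hazard ratio, which is a different quantity from the marginal one, and the need to fix in advance how unknown marker values are handled.
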